### 10.5 TRIAL REGISTRATION

The RAPID-NSTEMI trial will be registered on a recognised clinical trials database (clinicaltrials.gov) prior to recruitment commencing.

### 10.6 INSURANCE AND INDEMNITY

If the patient is harmed by taking part in this research project there are no specific indemnity and /or compensation arrangements. If a patient is harmed due to negligence, then the patient may have grounds for legal action, but they may have to pay for this. Regardless of this, if they wish to complain about any aspects of the way they have been treated or approached during the research project, the standard National Health Service complaint system will be available to them.

### 10.7 TRIAL MANAGEMENT GROUP (TMG)

Consisting of the Chief Investigator, Co-applicants, representatives of CTU and additional members as appropriate. The TMG will hold monthly meetings to ensure that the study runs smoothly and according to the pre-agreed timetable.

RAPID-NSTEMI Protocol v 4.0 | 01.08.2019 IRAS ID: 233921

33 of 71

RAPID-NSTEMI[figure not shown]

### 10.8 TRIAL STEERING COMMITTEE (TSC)

Consisting of at least three independent members, Chief Investigator, a representative of LCTU, representative of the Sponsor, representative of the funder and lay members will be convened. The TSC will be responsible for the scientific and ethical conduct of the study and will supervise progress of the trial. The independent Chair of the TSC will be [name]. The trial protocol and subsequent amendments will be approved by the TSC. The TSC members will be required to attend TSC meetings which will be held prior to the start of the trial and as required throughout the trial.

### 10.9 DATA SAFETY MONITORING COMMITTEE (DSMC)

An independent DSMC will be convened under the auspices of [name] and its own independent statistician and members appointed by [name]. The DSMC will convene annually to provide independent advice on study conduct and safety issues. Meetings will also be held as necessary should any urgent issues occur. The DSMC will develop a charter which describes the framework within which it will operate. It will meet to review data (blinded or un-blinded) provided by the LCTU and advise on whether the trial should be discontinued early for safety concerns.

### 10.10 CLINICAL EVENTS COMMITTEE (CEC)

A Clinical Events Review Committee (Chair [name]) will be established to determine whether a clinical event indicated by the site team is an appropriate clinical event. It will consist of a total of 3 experienced clinicians. Their reports will be used in the assessment of endpoints.

### 10.11 TRIAL CO-ORDINATION

Trial coordination will be provided by the Leicester Clinical Trials Unit (LCTU) in collaboration with the Chief Investigator and the Trial Management Group. LCTU is a dedicated, nationally registered trials unit (UKCRC No.43).

LCTU will be responsible for day to day management of the trial including the following: development of the protocol, ethical submissions, development of the specification for the data collection system, data management, meeting arrangements, quality assurance and preparation of trial documentation. LCTU will undertake site initiation visit, provide database training and provide essential documentation in the form of an Investigator Site File (ISF) which will also contain the Manual of Operations. The LCTU will ensure that the trial runs according to the pre-agreed timetable, ethical requirements are complied with, and that all aspects of the study are performed to the highest quality.

The LCTU will provide formal statistical support.

### 10.12 HEALTH ECONOMICS ANALYSIS

The cost-effectiveness analysis will be undertaken by researchers from the University of East Anglia, based on data collected as part of the study.

RAPID-NSTEMI[figure not shown]**10.13 CONSORT**

The trial will be reported in line with the CONSORT (Consolidated Standards of Reporting Trials) statement (Lancet 2001, 357: 1191-1194).

**10.14 DISSEMINATION & PUBLICATION POLICY**

Input from the trial's lay members will inform the dissemination plan for patients and public. Participants will be given a study newsletter when they attend their 12 month clinic visit providing information about the study timelines and when the study results will be known. Access to the findings of the study should be made available in a contemporary and user friendly way and full details of the results provided if the patient requests them.

The Chief Investigator will be responsible for ensuring that the results of the study are disseminated through peer review journals, conference presentations and local mechanisms at all participating centres irrespective of the outcome within 6 months after the database is locked. Authorship on the manuscript will be determined by the Chief Investigator according to contribution to the study after discussion with the Trial Steering Committee and according to the guidelines of leading medical journals. A full list of investigators shall be included in the original publication as an appendix. The TSC will be responsible for approval of all manuscripts arising from the study prior to submission for publication. All publications will quote the clinical trials registration number and will acknowledge the participating investigators, TSC and DSMC, LCTU, the Sponsor and the Funder.

No publication can be considered without the approval of the TSC.

**10.15 COMPETING INTERESTS**

None of the authors declare any competing interests.

**11.0 TRIAL TIMETABLE**

Anticipated project timeline:

Start up: August 2017 to May 2018: Protocol preparation, ethics submission documents prepared, study approvals, centre identification, centre invitations

Finalise protocol: May 2018 HRA & Ethical Committee application database set up, practical procedures, trial master files:

Site initiation visits and site training: August 2018- January 2019

First patient enrolment: September 2018.

Register trial on clinicaltrials.gov.org: June 2018

Principal Investigators Meeting at ACI: January 2018

Methods paper to be submitted: October 2019

Last patient enrolment: September 2020

Last follow-up: September 2021

Data Analysis: February 2022

Publication and Dissemination: September 2022

RAPID-NSTEMI

[figure not shown]

APPENDICES

APPENDIX I: GRACE SCORE

(Grace 2.0: Calculator [https://www.outcomes-umassmed.org/grace/acs\\_risk2/index.html](https://www.outcomes-umassmed.org/grace/acs_risk2/index.html))

|                             |                                            |
|-----------------------------|--------------------------------------------|
| Age                         | years                                      |
| Heart rate                  | bpm                                        |
| Systolic blood pressure     | mmHg                                       |
| CHF                         | Killip class                               |
| Diuretic usage              | No                                         |
| Creatinine                  | mg dL  / μmol L  |
| Renal failure               | No                                         |
| ST-segment deviation        | No                                         |
| Elevated troponin*          | No                                         |
| Cardiac arrest at admission | No                                         |

\* Or other necrosis cardiac biomarkers

Calculate

Reset

|                             |               |
|-----------------------------|---------------|
| Age                         | 72            |
| Heart rate                  | 110-129       |
| Systolic blood pressure     | 140-159       |
| CHF                         | Not available |
| Diuretic usage              | Yes           |
| Creatinine                  | Not available |
| Renal failure               | Yes           |
| ST-segment deviation        | No            |
| Elevated troponin*          | Yes           |
| Cardiac arrest at admission | No            |

\* Or other necrosis cardiac biomarkers

Calculate

Reset

If Killip Class and serum creatinine are not available, please ensure diuretic usage (current or historical) and renal failure fields are completed, as this impacts the final calculation.

[figure not shown]

RAPIDNSTEMI[figure not shown]**APPENDIX II: CLINICAL EVENT DEFINITIONS**

Full definitions will be provided after review by the Clinical Events Committee (CEC) in the CEC Charter, appropriate Case Report Forms and in the Manual of Operations.

**Death**

Death from any cause classified as cardiovascular or non-cardiovascular. Cardiovascular death includes any cardiac causes, or other vascular causes (e.g. pulmonary embolism, aortic dissection).

**Myocardial infarction (MI):**

Myocardial infarction will require a hospital admission with one or more of the following:

Type 1: Spontaneous re-MI: Recurrent angina symptoms or new ECG changes occurring before PCI or <48 hours from PCI that is compatible with re-MI associated with an elevation of CK-MB, Hs-Troponin-I/T, or total CK beyond ULN and 20% or more above the previous value.

Type 4a: CK-MB or total CK >3 times the ULN within 48 hours following PCI. If the pre-PCI CK-MB or total CK level is higher than the ULN, there also needs to be:

Either the demonstration of a falling CK-MB or total CK level prior to the onset of the suspected event, or a subsequent peak of the cardiac biomarker of at least 20% above the previous value obtained prior to the onset of the suspected event.

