somewhat flawed. For example so-called “early” PCI in some trials was not actually early at all: in the ICTUS (13,14) and TACTICS (6) trials, “early” PCI intervention was undertaken at a median time of 23 and 24 hours respectively, and in FRISC-II and RITA-3 trials (7,8) “early” PCI was actually very late indeed (median 96hrs). Furthermore, interpretation of trial outcomes is confounded by differing trial logistics, including trial inclusion criteria. Only 3 trials (see below) assessed really early intervention – of these, one was driven by non-clinical end points and another small study showed adverse outcomes in early intervention, contrary to all other trials. Specifically, in the ABOARD study (15) patients were randomised to immediate PCI or intervention the following day, but the primary end point was enzyme-determined infarct size, not clinical outcomes. Additionally, the lack of risk stratification could account for the demonstrated lack of difference even in the non-clinical endpoint. The OPTIMA study (16) compared immediate PCI versus PCI delayed for 24-48 hours and the incidence of 6 month primary end point (death, non-fatal MI, unplanned revascularisation) was significantly higher in the early group (intervention at median 25 minutes from randomisation) compared to those in the delayed (25 hour) group (RR=1.5, 95% CI=1.10-2.07, p=0.008). This small study (n=140) suggests a case could be made for so-called “pharmacological passivation” prior to PCI. However, nearly all of the end-point difference occurred in the acute stages, suggesting perhaps it was acute events (i.e. PCI related events) that drove any differences. In the LIPSIA-NSTEMI-ACS study there was no significant difference between immediate (within 2hr) and early (within 24hrs) PCI in higher-risk N-STEMI ACS patients with GRACE score >140. However, again this study was not powered to detect differences in clinical events; only differences in CK-MB (17). The best study, the RIDDLE N-STEMI trial, randomised 323 N-STEMI ACS patients to receive either immediate (<2h from randomisation) or delayed (2-72hr, median time in trial 61hr) PCI (18). This relatively small trial showed 30-day primary endpoint of death or new MI was lower in the immediate PCI group (4.3% vs. 13%, HR=0.32, 95% CI=0.17-0.67, p=0.002). This difference was driven by re-infarction in the delayed PCI group while awaiting angiography. There was no difference in the composite endpoint in a landmark analysis from 31days-1yr. Again, this trial was underpowered to detect new MI post-discharge and also to detect any impact on death up to 1 year post N-STEMI ACS. As with all of the studies quoted above, GRACE score was not used as a criteria for enrolment and only 36% of the study population retrospectively had a GRACE score >140.

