### 7.2 OUTCOME MEASURES (for definitions see APPENDIX II)

#### 7.2.1 Primary clinical outcome

Incidence of the composite of **all-cause mortality, new myocardial infarction and admission for heart failure** within **12 months** following randomisation.

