#### 7.2.2 Secondary Outcome Measures

- Individual components of the primary end-point within 12 months:
  - Incidence of all-cause mortality within 12 months
  - Incidence of new myocardial infarction within 12 months
  - Incidence of admission for heart failure within 12 months
- Incidence of cardiovascular mortality within 12 months
- Length of in-patient stay (defined as randomisation to first discharge) in days
- Events prior to planned procedure:
  - Incidence of all-cause mortality prior to planned coronary angiography following index admission with NSTEMI
  - Incidence of new myocardial infarction prior to planned coronary angiography following index admission with NSTEMI
  - Incidence of major bleeding (classified as BARC 3-5) prior to planned coronary angiography following index admission with NSTEMI
- Incidence of admission for ischaemia-driven revascularisation within 12 months
- Incidence of admission for any cause within 12 months
- Quality of life measured using Seattle angina score at 24 hours post procedure, 1 month, 6 months and 12 months
- Quality of life as assessed using the EQ-5D-5L questionnaire at 24 hours post procedure, 1 month, 6 months and 12 months
- Incidence of BARC 3-5 classified bleeding as in-patient, and up to 12 months
- Incidence of stroke within 12 months

RAPID-NSTEMI[figure not shown]

- Cost effectiveness of immediate PCI versus standard care
- Left ventricular ejection fraction (LVEF) and infarct size on cardiac MRI scan\*
- Sensitivity and specificity of novel biomarkers in predicting which patients do or do not require PCI following diagnostic angiography\*\*
- Proportion of patients needing emergency/urgent revascularisation (in group B)
- Incidence of total VARC-2 classified access site complications as in-patient, and up to 12 months
- Incidence of major VARC-2 classified access site complications as in-patient, and up to 12 months

\*Additional CMR outcomes are specified in the CMR substudy protocol (appendix V)

\*\* Additional biomarker outcomes are specified in the Biomarkers substudy protocol (appendix VI)

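### Appendix II has no MI category for a spontaneous MI from 48 hours after PCI to 12 months, although the primary endpoint counts new MI over the whole 12 months.

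*Protocol*

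**What the plan says.** Section 7.2.1 of the protocol defines the primary outcome as the composite of all-cause death, new MI and heart-failure admission within 12 months of randomisation. Section 7.2.2 repeats the MI component as a secondary outcome: "Incidence of new myocardial infarction within 12 months". The Section 7.2 heading refers the reader to Appendix II for definitions.

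The MI entry in Appendix II opens with a general condition: "Myocardial infarction will require a hospital admission with one or more of the following". Two types follow.

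- Type 1 (spontaneous): "Recurrent angina symptoms or new ECG changes occurring before PCI or <48 hours from PCI", with CK-MB, Hs-troponin or total CK above the upper limit of normal (ULN) and at least 20% above the previous value.
- Type 4a (procedural): "Type 4a: CK-MB or total CK >3 times the ULN within 48 hours following PCI", with further conditions if the pre-PCI value was already raised.

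No other MI type is listed. Appendix II begins by saying that fuller text will come later: "Full definitions will be provided after review by the Clinical Events Committee (CEC) in the CEC Charter, appropriate Case Report Forms and in the Manual".

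**The concern.** The endpoint and its definition cover different periods. Both MI types close 48 hours after PCI, while the endpoint runs to month 12. An adjudicator applying Appendix II to a patient who had PCI and then a spontaneous MI at, say, month 4 would find no category for it.

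Two things are at stake. First, MI is one of three components of the primary composite, and the trial is open-label. A rule that has to be stretched to count an ordinary late MI leaves the decision to judgement made with the allocation known at site. Second, the countable period is tied to PCI, and the time to PCI is what is randomised. The period in which a spontaneous MI can count therefore differs by arm. Section 6.3 criticises an earlier timing trial for applying different MI definitions to its two groups. A PCI-anchored window brings in a milder form of the same problem.

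**Working it through.** **1. Coverage for a patient treated by PCI.** I take PCI in the definition to mean the index procedure.

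| Period | Type 1 | Type 4a | In the 12-month endpoint |
|---|---|---|---|
| Randomisation to PCI | yes | no | yes |
| 0 to 48 h after PCI | yes | yes | yes |
| 48 h after PCI to month 12 | no | no | yes |

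The third row is the gap.

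**2. Length of the countable window by arm.** Inputs: transfer in Group A is recommended, not mandated, within 90 minutes of randomisation (Section 7.4). The 2015 audit median time to angiography for direct admissions is 60.8 hours (Section 7.4), which I assume runs from admission. Randomisation is within 6 hours of admission (Section 7.3.1).

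- Group A: 1.5 + 48 = 49.5 h.
- Group B: (60.8 − 6) + 48 = 102.8 h, up to 60.8 + 48 = 108.8 h.
- Ratio: 102.8/49.5 = 2.1 to 108.8/49.5 = 2.2.

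For example, a spontaneous MI at hour 72 would not count in a Group A patient treated at hour 2, but would count in a Group B patient still waiting. Taken alone, this asymmetry favours immediate angiography. Against 8,760 hours in a year, even the longer window is 108.8/8,760 = 1.2% of follow-up. That is a share of time, not of MIs.

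**3. The protocol's own sample size.** Inputs (Section 8.1): 19% against 14.25%, two-sided α = 0.05, 80% power, chi-squared test of proportions.

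n per arm = [1.960·√(2·p̄·(1−p̄)) + 0.842·√(p₁(1−p₁) + p₂(1−p₂))]² / (p₁−p₂)²

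With p̄ = 0.16625: (1.960×0.5265 + 0.842×0.5254)² / 0.0475² = 963.2, so 964. The stated figure reproduces, and power at 964 is 80.0%.

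**4. Sensitivity.** The protocol gives neither the MI share of the 19% nor the timing of MIs, so the points lost (m) are an assumption. They stand for patients whose only primary event is an uncounted late MI. A patient who also dies or is admitted with heart failure still counts.

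Power = Φ{[(p₁−p₂)·√n − 1.960·√(2·p̄·(1−p̄))] / √(p₁(1−p₁) + p₂(1−p₂))}, n = 964.

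For m = 3 with the 25% reduction kept (16% against 12%): (0.04×31.05 − 1.960×0.4907)/0.4899 = 0.572, power 71.6%. For m = 3 with no treatment effect on the lost MIs (16% against 11.25%): (0.0475×31.05 − 1.960×0.4852)/0.4840 = 1.083, power 86.0%.

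| m (points) | Control rate | Power, 25% relative reduction kept | n per arm for 80% power, 25% kept | Power, lost MIs carry no effect |
|---|---|---|---|---|
| 0 | 19% | 80.0% | 964 | 80.0% |
| 1 | 18% | 77.4% | 1028 | 82.0% |
| 2 | 17% | 74.6% | 1100 | 84.0% |
| 3 | 16% | 71.6% | 1181 | 86.0% |
| 4 | 15% | 68.4% | 1272 | 88.2% |
| 5 | 14% | 65.0% | 1377 | 90.3% |

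The sign of the effect on power depends on whether late MIs respond to treatment, which the protocol does not settle.

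**The case against.** **The appendix is provisional.** It says that full definitions will follow in the CEC charter, the CRFs and the Manual of Operations, and Section 10.10 provides for committee review. Those documents are not shown and may already close the gap. The less-than sign may also be a slip for greater-than, though nothing in the protocol proves it. This lowers the likely practical damage. It does not withdraw the printed rule: a charter that counts late MIs would contradict the appendix, and one that copies it would omit them.

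**A reader might infer that most 12-month MIs are lost.** The documents do not support that, because they give no MI timing. The 323-patient timing trial described in Section 6.0 points to early events: "This difference was driven by re-infarction in the delayed PCI group while awaiting angiography", which is inside the window, and "There was no difference in the composite endpoint in a landmark analysis from 31days-1yr". The biomarker substudy expects about one-third of patients not to need PCI, and for them the pre-PCI limb can be read as covering all of follow-up.

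**A reader might also infer that the admission condition excludes MIs during the index stay.** That reading would nearly empty the definition. Type 4a falls within 48 hours of PCI, and Section 7.2.2 lists new MI before planned angiography as an outcome, so index-stay events are plainly meant to count. What stands is an ambiguity: the text does not say whether the index admission satisfies the condition.

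**A reader might infer a definite loss of power.** The last column of the table shows the opposite under an equally possible assumption.

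**Conclusion.** The point holds as a contradiction in the definition of a primary-endpoint component. For patients treated by PCI, Appendix II provides no MI category from 48 hours after PCI to month 12, while Sections 7.2.1 and 7.2.2 count MI throughout. The countable window is also about twice as long in Group B as in Group A, given the audit median and the recommended Group A transfer time. The number of MIs affected and the net effect on power cannot be established from the protocol. For 1 to 5 points lost, power at 964 per arm ranges from 77% down to 65% if the 25% relative reduction persists, and from 82% up to 90% if the lost MIs carry no effect. The case for correction rests on the contradiction and the unequal window, not on a power figure.

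**What to change.** In Appendix II:

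1. State that Type 1 applies at any time from randomisation to 12 months, in patients with or without PCI.
2. Keep the existing symptom/ECG plus biomarker route for the first 48 hours after PCI, alongside Type 4a. Leaving that period to Type 4a alone would open a new gap. Type 4a needs CK-MB or total CK, whereas the scheduled cardiac biomarker in Tables 1 and 2 and Section 7.10 is Hs-troponin, so symptomatic, troponin-confirmed re-infarctions that count now could be lost.
3. Say what replaces the 20% rise over the previous value when a late event has no recent value to compare with.
4. Replace the general condition with one under which an MI counts if it occurs during the index admission or leads to a new admission.

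Put the same text in the CEC charter, CRFs and Manual of Operations. Then re-review any reported MIs that were classified under the restricted window. Include late events that sites may have filed under another heading, such as recurrent ischaemia or cardiovascular admission (both listed in Section 7.15.5).

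The cost is a wording amendment and a limited round of adjudication. MACE status is already collected at 30 days, 6 months and 12 months, so no new visits are needed. Some source documents may have to be retrieved if sites used the printed window to decide what to submit.

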### 7.3 ELIGIBILITY

#### 7.3.1 Inclusion Criteria

- 18 years of age and over
- Patients presenting to hospitals with a clinical diagnosis of non-ST elevation myocardial infarction comprising:
  - Ischaemic symptoms (as defined in Appendix III)
  - Elevated high sensitivity Troponin T or I (above the normal range for individual hospitals)
- GRACE-2.0 score ([www.gracescore.org](http://www.gracescore.org)) of either:
  - $\geq 118$  (corresponding to 6-month death  $>6\%$ ) OR
  - $\geq 90$  but  $<118$  (corresponding to 6-month death  $>3\%$  but  $<6\%$ )
- If GRACE 2.0 score  $\geq 90$  or  $<118$  must have at least one additional high risk feature:
  - Anterior location of ECG changes (leads V2 – V5)
  - ST-segment depression in 2 contiguous leads (any territory) of 0.15mV/ 1.5mm
  - Diabetes Mellitus on medication
  - High-sensitivity Troponin I or T 3 x ULN
- Onset of ischaemic symptoms at any time prior to admission but most recent episode within 12 hours prior to admission
- Intention to perform angiography and, if indicated, follow-on revascularisation
- Provision of assent or written consent
- Randomisation must be performed within 6 hours of admission

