#### 7.3.2 Exclusion Criteria

- ST elevation myocardial infarction
- Evident type 2 myocardial infarction (e.g. anaemia)
- Evidence of previous known cardiomyopathy
- Cardiogenic Shock
- Known severe valvular heart disease
- Need for urgent PCI according to ESC Guidelines (haemodynamic instability, VT/VF, recurrent or persistent pain)
- Any contraindication to PCI
- Current participation in another intervention trial

RAPID-NSTEMI

[figure not shown]

Figure 2: Patient Flow to Randomisation

[figure not shown]

\*or written consent, depending on local regulatory guidelines (applicable to sites in Northern Ireland/Scotland only)

RAPID-NSTEMI[figure not shown]**7.4 TRIAL INTERVENTIONS**

If the initial clinical eligibility for N-STEMI criteria are suspected, blood is drawn for Hs-Troponin immediately (i.e. as close to admission as possible). If this returns raised according to individual hospitals criteria then a GRACE 2.0 score is calculated at that time. A GRACE 2.0 score of  $\geq 118$ , or  $\geq 90$  with additional high risk features - see inclusion criteria, will lead to patient ASSENT (or written informed consent, depending on local regulatory guidelines. Further details are provided in section 7.6) and if confirmed then randomisation providing there are no exclusion criteria. If the initial Hs-Troponin is reported as normal, a second sample may be taken at 3 hours in line with current European guidelines. If elevated, the participant may be randomised if all other criteria met. Randomisation will be performed using an independent Interactive Voice Response System randomisation system (Sealed Envelope Ltd), the patient will be randomised to either Group A or B. The participant trial number will be documented.

**GROUP A:** Immediate angiography with follow-on revascularisation if indicated - transfer to the catheter laboratory should be performed as soon as possible, and is recommended but not mandated within 90 minutes of randomisation

**GROUP B:** Standard angiography with follow on revascularisation if indicated, - within Guideline recommended times.  
Standard interim therapy such as LMWH/DAPT will be mandated in this group until angiography.

All interventional procedures will be undertaken according to current best practice (e.g. peri-procedural intravenous heparin, radial approach as preferred access site, and use of drug-eluting stents). Patients in Group B who suffer the following:-

- on-going chest pain,

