- recurrent dynamic ECG changes
- haemodynamic instability during the wait till angiography

will be allowed to cross to earlier angiography +/- revascularisation as per best clinical practice. Reasons for cross-over will be carefully documented. Crossover rates will be carefully monitored for accuracy but if crossover occurs, this will be measured as a secondary end-point.

We have considered carefully whether this design will allow sufficient temporal separation between the two groups enabling robust interpretation of the results. According to the 2015 BCIS audit returns, the median time to angiography for patients (directly) admitted to a PCI-capable centre with N-STEMI ACS = 60.8 hours, and for inter-hospital transfer = 82.1 hrs. Apart for one outlier the earliest time for the direct admission patients appears to be in the order of 26 hours. The risk of time contamination between groups A and B will be minimised by strict trial discipline; without this discipline the study will be difficult to interpret and will not be robust. The “times to intervention” will be important trial audit measures. All recruiting sites will be asked to treat the standard care arm participants according to their

RAPID-NSTEMI[figure not shown]

NHS Trust's current practice. To reduce time delay in Group A only trial sites with on-site cath labs will be included.

All patients will be included in a within-trial cost effectiveness analysis.

A mechanistic CMR sub-study of 200 patients (100 from each group) will evaluate LV function, and differences in infarct size (especially the impact of Type 4a MIs) between groups (APPENDIX V).

A biomarkers substudy will investigate if novel biomarkers can predict the need for PCI and future clinical outcomes (APPENDIX VI)

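### The either/or test for Type 4a MI can count injury from the index infarct as a new MI, at rates that may differ by arm because PCI timing is what is randomised

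*Protocol*

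**What the plan says.** Under Myocardial infarction in Appendix II, Type 4a starts from a marker threshold: "CK-MB or total CK >3 times the ULN within 48 hours following PCI". A further condition applies only to patients whose marker was raised beforehand: "If the pre-PCI CK-MB or total CK level is higher than the ULN, there also needs to be" one of two things. The wording is "Either the demonstration of a falling CK-MB or total CK level prior to the onset of the suspected event, or a subsequent peak", and the second limb reads in full "a subsequent peak of the cardiac biomarker of at least 20% above the previous value obtained prior to the onset of the suspected event". The connecting word is 'or', so either is enough. If the pre-PCI level is not above the ULN, the threshold alone decides. Unlike Type 1 in the same appendix, Type 4a mentions neither symptoms nor ECG change.

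New MI is part of the primary outcome in section 7.2.1: "Incidence of the composite of all-cause mortality, new myocardial infarction and admission for heart failure within 12 months following randomisation".

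The arms differ by design in when PCI happens. Patients enter with their "most recent episode within 12 hours prior to admission" and are randomised within 6 hours of admission (section 7.3.1). For Group A, transfer to the laboratory "is recommended but not mandated within 90 minutes of randomisation" (section 7.4). For Group B, section 7.4 cites audit data: "the median time to angiography for patients (directly) admitted to a PCI-capable centre with N-STEMI ACS = 60.8 hours", with the earliest direct admissions at about 26 hours.

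Scheduled sampling also differs. Tables 1 and 2 give Group A one troponin before the procedure (admission) and Group B two (admission and pre-angiography). Neither CK-MB nor total CK appears in Table 2 or among the post-PCI bloods in section 7.10. Appendix II leaves full definitions to the CEC charter, case report forms and Manual of Operations, which are not shown.

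**The concern.** A Type 4a rule for patients already having an infarct has to separate new procedural injury from the injury that brought them in. This one does not, on either limb. Each limb is met by an index marker at a different stage of its course, and the randomised intervention determines the stage at which PCI is done. The error is therefore tied to allocation.

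If more index injury is counted in Group A, a true benefit is diluted or an apparent harm created. If more is counted in Group B, a benefit is exaggerated or created. Even equal error in both arms dilutes the contrast. It would also blur the comparison of Type 4a injury, which section 6.2 gives as a reason why delay might help and section 7.4 names as a target of the CMR sub-study.

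**Working it through.** **1. The rule applied to an uneventful PCI (pre-PCI marker above ULN, post-PCI value above 3 x ULN).**

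| State of the index marker at PCI | Falling limb | 20% limb | Counted as Type 4a? |
|---|---|---|---|
| Still rising, later peak at least 20% higher | not met | met | yes |
| Past its peak and declining | met | not met | yes |
| Flat, no fall and no 20% rise | not met | not met | no |

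The first two rows contain no new injury, yet both count.

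**2. Which arm is in which row.** A Group A patient randomised at the 6-hour limit and moved within the recommended 90 minutes reaches the laboratory by 6 + 1.5 = 7.5 hours after admission. Group B is expected at a median of 60.8 hours. The rising row is therefore more likely in Group A and the declining row in Group B. This is an inference: the protocol gives no CK or CK-MB time course, although the rationale in Appendix V does presume necrosis that continues until reperfusion.

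**3. The plan's own sample size.** Inputs from section 8.1: 19% v 14.25%, two-sided alpha 0.05, power 80%.

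n = [1.96 √(2 p̄(1 − p̄)) + 0.8416 √(pA(1 − pA) + pB(1 − pB))]² / (pB − pA)², with p̄ = 0.16625

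= (1.0320 + 0.4422)² / 0.0475² = 963.2, so 964 per arm. The stated 964 is reproduced, and power at 964 is 80.0%.

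**4. Illustration of sensitivity.** Assumptions: two-thirds of patients have PCI (the expectation in the biomarker sub-study, Appendix VI section 4, carried over to the whole trial). A share f of Group A PCI patients otherwise free of events is misclassified, and q times that share in Group B. Neither f nor q is in the documents.

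pA' = 0.1425 + 0.8575 × (2/3) × f

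pB' = 0.19 + 0.81 × (2/3) × f × q

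For f = 5%: pA' = 0.1425 + 0.0286 = 17.1%. For q = 0.5: pB' = 0.19 + 0.0135 = 20.35%. For q = 1: pB' = 0.19 + 0.027 = 21.7%.

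Power = Φ[(|pB' − pA'| − 1.96 SE₀)/SE₁], with SE₀ pooled, SE₁ unpooled and 964 per arm.

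| f in Group A | q | Group A | Group B | Relative risk reduction | Power |
|---|---|---|---|---|---|
| 0 | – | 14.25% | 19.0% | 25% | 80% |
| 3% | 0 | 16.0% | 19.0% | 16% | 42% |
| 3% | 0.5 | 16.0% | 19.8% | 19% | 60% |
| 3% | 1 | 16.0% | 20.6% | 23% | 75% |
| 5% | 0 | 17.1% | 19.0% | 10% | 19% |
| 5% | 0.5 | 17.1% | 20.35% | 16% | 45% |
| 5% | 1 | 17.1% | 21.7% | 21% | 72% |

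**5. No true effect (19% in both arms).** If 5% of PCI patients in one arm only are misclassified, that arm shows 0.19 + 0.81 × (2/3) × 0.05 = 21.7% v 19%. The chance of a significant difference at 964 per arm is about 31%. It counts against Group A if the error sits there and, by symmetry, in favour of Group A if it sits in Group B.

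**The case against.** A reader might infer that the rule adds false events almost only to Group A, so that the trial is biased against immediate angiography and its power could fall to 19%. The text does not support that. A Group B patient past the peak satisfies the falling limb, which is sufficient alone once the marker exceeds three times the ULN. The 19% figure holds only if Group B misclassification is set to zero.

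Three further objections limit the point.

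- **Timing.** Symptom onset may be at any time before admission, and the 90-minute target is not mandatory, so not every Group A patient has a rising marker. Nor do the documents show how often an index CK exceeds three times the ULN: entry is on troponin. This stands, and it leaves f unknown.
- **Collection.** The threshold is on CK-MB or total CK, and neither is scheduled. The rule operates only where a site measures them outside the schedule. This stands as a limit on frequency, but it makes ascertainment depend on local habit and does not make the rule sound.
- **Adjudication.** The CEC decides whether a reported event is appropriate (section 10.10), and full definitions are left to its charter. This stands in part: an uneventful PCI does not automatically become an endpoint. But the only rule written in the protocol tells the committee to count these cases.

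**Conclusion.** The concern holds as a fault in the definition. Both limbs admit index-infarct injury as new MI, new MI is in the primary composite, and the stage of the index marker at PCI depends on the randomised timing. That the error can differ by arm follows from the wording and the protocol's timings, together with the ordinary expectation that a marker rises and then falls.

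Net direction and size cannot be derived. There is no marker time course, no misclassification rate and no scheduled CK or CK-MB. The power figures (from 80% down to 19%, 45% or 72% at an assumed 5% in Group A) show only that the result is sensitive to small rates and to the balance between arms. They are not a forecast, and a one-sided bias against Group A should not be claimed. This should be fixed before adjudication; it does not by itself invalidate the design.

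**What to change.** In Appendix II and the CEC charter:

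- Replace the either/or. When the pre-PCI marker is raised, require both a stable or falling pre-PCI marker and a post-PCI peak at least 20% above the last pre-PCI value, besides the existing threshold.
- For every Type 4a event in both arms, also require corroboration: new ischaemic ECG change or a documented angiographic complication.
- Where a stable or falling marker cannot be shown, let that corroboration with the threshold and the 20% rise suffice.
- Have the CEC adjudicate these events masked to allocation as far as possible.

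The second and third items matter. With the 'and' rule alone, or with a rule that rejects marker-only events when there is a single pre-PCI value, marker-only Type 4a would be countable in Group B (two scheduled pre-procedure samples) and almost never in Group A (one). That would exchange one asymmetry for another. Under the full rule the 20% rise and the corroboration decide in both arms, and the pre-PCI trend is supporting evidence. Table 2 schedules a pre-angiography ECG for Group B only, so the charter should name a comparison ECG that exists in both arms, such as the one on admission.

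The cost is wording. ECGs and procedural details are already recorded (Table 2, section 7.10), so no new procedure is needed. Some true marker-only Type 4a events will not count, in both arms alike.
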